## Justification of choice of study population

We will divide our 30 subjects into three different population groups. The first group is the group of 10 able-bodied subjects who will act as a control for our spinal cord injured subjects. These subjects have to be healthy and physically active but they are no elite athletes.

The second group of population will be the paraplegic subjects injured below Th8. Their spinal cord injury is sensory and motoric complete (AIS A). As the innervation of the heart and thus the regulation of heart rate is located around Th1 to Th6, we can be certain, that their heart is normally innervated. That means we should identify the same or almost the same outcome for HRV as for our able-bodied subjects. It will be very interesting to see the differences in the action of caffeine on the ANS but also on exercise performance compared to able-bodied subjects.

The third population group represents our tetraplegic subjects. They will be injured between C5 and C7 in a sensory and motoric complete way (AIS A). With the inclusion of this population we are sure, that these subjects are able to handle an arm crank ergometer and that their autonomic innervation of the heart is disturbed.

# STUDY OBJECTIVES

## Overall Objective

The overall objective of this study is to understand the influence of caffeine on HRV and on exercise performance of these different population groups especially the effects on the tetraplegic and paraplegic subjects. So, we want to know whether caffeine acts as an ergogenic aid over a 3 min all out test in spinal cord injured subjects and if HRV is altered through the ingestion of caffeine. It is possible that the low frequency component of the HRV does not alter in tetraplegic subjects due to the missing sympathetic innervation of the heart.

## Primary Objective

**Primary objective for HRV:** First of all we try to find out if caffeine supplementation alters the HRV at rest. From previous literature it is clearly stated that caffeine activates sympathetic nerves through the distribution of epinephrine and norepinephrine [31]. As in the HRV we can differentiate between components reflecting sympathetic and parasympathetic nerve activation, HRV should alter after the intake of caffeine supplementation. In our tetraplegic subjects there is a lack in the sympathetic innervation. Therefore, it is possible, that HRV or more precisely the sympathetic component of the HRV does not alter after the intake of caffeine. The following questions arise: What is the difference between paraplegic and able-bodied subjects in HRV after caffeine supplementation? Are there any differences comparing paraplegic, able-bodied and tetraplegic subjects with each other? Or does caffeine even not influence HRV in these different population groups?

**Primary objective for exercise performance:** Our aim is to investigate if caffeine enhances exercise performance in a 3 min exercise test at the arm crank ergometer. As studies with able-bodied subjects already showed some performance enhancing effects our focus lays on the spinal cord injured populations. Due to physiological adaptations after the spinal cord injury gut motility is slowed down and ANS activity is impaired. Therefore, absorption and also action of caffeine may be altered or even retarded. That`s why we want to know, if caffeine shows the same ergogenic effects on exercise performance in the spinal cord injured population as it shows in able-bodied subjects.

## Secondary Objectives

As secondary objectives we want to test if caffeine increases catecholamine concentrations in the bloodstream in all three population groups and if there are any differences between these three groups.

## Safety Objectives

The study aims to assess the tolerability of caffeine in spinal cord injured subjects in terms of gastrointestinal and other side effects.

# STUDY OUTCOMES

## Primary Outcome

**Heart rate variability:** HRV difference between the measurement before the ingestion of caffeine compared to the measurement one hour after the ingestion of caffeine. This primary outcome gives us some further information about the effect of caffeine on the HRV and shows the differences between our three population groups.

**Exercise performance test:** We want to compare the power output between the two tests (placebo vs. caffeine) to know whether caffeine shows some ergogenic effects in the spinal cord injured population groups concerning arm crank exercise performance. To date, only one study examined exercise performance tests with the spinal cord injured population groups using caffeine as a supplementation [17]. These findings would provide some further information about caffeine supplementation in wheelchair sports.

## Secondary Outcomes

**HRV:** As a secondary outcome we try to compare HRV baseline measurement with the measurement after the exercise test. As we know from previous data, HRV should be altered after an exercise performance and could be influenced by the ingestion of caffeine.

**Catecholamines:** We will compare epinephrine and norepinephrine concentrations before the ingestion of any supplement with the concentrations one hour after the ingestion of the supplements. As some previous studies showed no effect of caffeine on epinephrine and norepinephrine concentrations in tetraplegic patients, it will be very interesting to see these results and to compare it to our HRV and performance exercise testing.

## Other Outcomes of Interest

**Blood pressure:** We will compare the baseline measurement of diastolic and systolic blood pressure before the ingestion of any supplement with the measurement one hour after the ingestion of the supplement. Maybe spinal cord injured subjects could benefit from the ingestion of caffeine with a faster blood pressure adaptation if they have to transfer from the supine to the sitting position.

**Heart rate:** We will compare heart rate during the exercise test between the two different supplementation trials (placebo vs. caffeine). As caffeine acts as a stimulant heart rate may be altered after the ingestion of caffeine compared to placebo.

**Rate of perceived exertion (RPE):** We will compare the RPE after the exercise performance test between the two intervention trials (placebo vs. caffeine). As caffeine is well known as a pain decreasing agent it is possible that RPE is lowered after the ingestion of caffeine compared to placebo.

**Tidal volume:** We intend to investigate the difference between the tidal volume during the HRV measurement before the ingestion of any supplement with the measurement one hour after the ingestion of the supplement. As caffeine shows some bronchodilatation effects it is possible that at the same breathing frequency the tidal volume is increased after the ingestion of caffeine compared to placebo.

**Lactate concentration:** As another outcome of interest we measure lactate concentration after the warm up, to control if the subject didn`t warm up too hard and to check that their warm up didn`t differ between the placebo and the caffeine trial. After the exercise performance test we will measure lactate concentration for a second time. We might see differences in lactate concentration between the two trials if they reach a higher power output in one of the two trials or maybe they can suffer more because of a reduced pain perception after the caffeine ingestion and that could possibly result in a higher lactate concentration.

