## Methods of minimising bias

### Randomisation

Randomisation will be assessed by lot. 50 % of all the subjects will first conduct the placebo trial and the other 50% first the caffeine trial. With which trial they start will be assigned by lot. So, there will be an “A” lot and a “B” lot and the fortune will decide whether they have the A or the B trial first. The test administrator only knows whether they have to ingest supplement A or supplement B but he does not know which supplement it is.

Applying a significance level of 0.05 and a power of 0.8 with a difference of 7.59 and a standard deviation of 10 Watt, we receive a total sample size of 9. With inclusion of a 10% drop-out rate we obtain a total sample size of 10 subjects per group. With the three different groups (able-bodied, paraplegic and tetraplegic subjects) we have in total 30 subjects and thus 120 visits overall.

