### Assessment of other outcomes of interest

**Blood Pressure:** This parameter assesses the arterial blood pressure during the systolic and diastolic phase of the heart cycle. The blood pressure will be assessed twice. The first measurement takes place before ingestion of capsules in the 9^th^ minute of the relaxing phase of HRV measurement. The second measurement takes place again in the 9^th^ minute of the relaxing phase but of the second HRV measurement. A blood pressure monitor is used. The subject is in a supine position. The blood pressure is assessed only once at each measurement point.

**Heart rate:** This parameter assess the heart beats per minute and is measured during the HRV measurement and during the performance testing using the Polar heart rate monitor (Polar, Kempele, Finland). The heart rate during the HRV measurement are saved on the watch and will later be transferred on the computer. The values during the performance test will be directly transcribed on the CRF.

**Rate of perceived exertion (RPE):** The RPE scale is a method to measure subjectively the intensity of perceived exertion. The scale, called the Borg scale, runs from 6 to 20, whereas 6 represents no physical exertion and 20 represents a maximal exertion. The RPE will be assessed after warming up and after the 3 min performance test. The subject will be requested to rank verbally the intensity of warming up respectively of the performance test on the Borg scale.

**Tidal volume:** The tidal volume is used for measuring the breathing volume during normal inhalation and exhalation without any extra effort of the subject. This parameter is assessed during the three HRV measurements at the beginning of the testing procedure, after the 40 min break and after the 5 min break due to the performance testing. During the all out 3 min test, the respiratory parameters are recorded as well. The subject puts on a breathing mask which is connected to a spirometer (MetaMax 3B,Cortex Biophysik GmbH, Leipzig, Germany). The average volume during the time period of the HRV measurement is recorded.

**Lactate:** Measurement of lactate in the blood will be done twice during one experiment. The first time after the warm-up period on the arm crank ergometer (Angio V2, Lode, Groningen, Netherlands) and the second time after the 3 min performance test. The concentration of lactate will directly be measured by blood lactate analyzer (Biosen, EKF diagnostic, Cardiff, Great Britain).

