# STATISTICAL METHODS

This study is a pilot-study with a small sample size. Therefore, normal distribution of the data cannot be assumed. Descriptive statistics, i.e. median, 25/75% quartiles, 95% confidence intervals and range, will be used. A p-value of < 0.05 will be considered significant, even though multiple hypotheses will be tested.

The treatment period (i.e. sequence of placebo and caffeine treatment) will not be included into the statistical analysis, because the wash-out period (48h) is considered more than long enough to prevent any carry-over effect. Furthermore, the period effect is considered to be negligible, because study participants will undergo a training session before the collection of data in order to avoid any learning effect.

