### Secondary Analyses

The correlation between HRV and performance under caffeine will be evaluated with the Spearman's rank correlation coefficient.

Changes in tidal volume, blood pressure and epinephrine and norepinephrine blood concentration from baseline to post-treatment values will be compared between placebo and caffeine treatment using the Wilcoxon signed-rank test.

Changes in lactate blood concentration under treatment before and during performance testing will be compared between placebo and caffeine treatment using the Wilcoxon signed-rank test.

Changes in tidal volume and HRV under treatment before and after performance testing will be compared between placebo and caffeine treatment using the Wilcoxon signed-rank test.

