# QUALITY ASSURANCE AND CONTROL

## Data handling and record keeping / archiving

### Case Report Forms

All data are recorded with a paper CRF except the HRV values, heart rate during HRV measurement and the catecholamine concentration. These values will be directly transferred in secuTrial after analysing on a computer respectively in a laboratory. For each enrolled study participant a CRF is maintained and the CRF is kept current to reflect subject status at each phase during the course of the study. Subjects cannot be identified in the CRF by name or initials and birth date. The following coded identification is used: for example HRV_T_01, which means the subjects will be identified by his belonging to the group (paraplegic, tetraplegic or able-bodied group) and a number which identifies him within the group.

Every staff member is authorized for any CRF entry and by initials noted on the CRF the investigator can be subsequently identified. The data on the CRF will later be entered in the secuTrial database (iAS, Berlin, Germany). So a double data entry will occur.

One person will enter the data from the CRF paper form into the secuTrial database. A second person will control the correctness of the data in the secuTrial and the principal investigator will finally release the data for archival storage.

The Clinical Trial Unit will only give access to three people: [name] and [name] will get access for data entering and controlling and the principal investigator [name] for data release.

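### Section 11.4.5 declares safety analysis not applicable although section 4.4 sets a tolerability objective, and the withdrawal and completer rules would drop the men who tolerate caffeine worst

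*Protocol*

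**What the plan says.** The safety objective in section 4.4 reads: "The study aims to assess the tolerability of caffeine in spinal cord injured subjects in terms of gastrointestinal and other side effects". Data are collected for it. Section 9.2.4 has each man asked about tolerance and gastrointestinal problems 45 min after the capsules. Section 5.4 has him asked about side effects again after every test session. Section 10.1.2 puts the events on the CRF. Because of the crossover, each man who finishes gives this information once under caffeine and once under placebo.

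Section 11.4.5, the place for the safety analysis, says only that it is not applicable.

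Five other sections decide whose data survive:

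- 7.4 withdraws a man who has pronounced gastrointestinal side effects or worse problems from the caffeine.
- 8.3 excludes a man who has any problem with the ingested dose.
- 8.5 leaves withdrawn men's data out of the analysis and has what was collected destroyed.
- 11.4.1 analyses only men who completed the whole protocol.
- 11.5 replaces drop-outs with new participants.

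Against 8.5, section 12.1.3 requires all study data to be archived for at least 10 years, and section 12.2.3 says electronic data will not be deleted.

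Heart rate, which is also monitored for safety (5.4), has a treatment comparison of its own among the other outcomes in section 5.3: "We will compare heart rate during the exercise test between the two different supplementation trials (placebo vs. caffeine".

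**The concern.** An objective with planned data collection should lead to a stated result. Here the section that should supply it rules it out. This is not detail left for a later analysis plan: the protocol makes a positive statement that contradicts its own objective.

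The second problem is selection. Withdrawal under 7.4 and 8.3 depends on the outcome that 4.4 sets out to assess. If those men's records are destroyed and their places refilled, a tolerability summary made from what remains leans towards good tolerability. At stake is what the study can say about side effects of 6 mg/kg caffeine in spinal cord injured men. The two primary hypotheses are not affected by the missing safety analysis.

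**Working it through.** The protocol gives no tolerability figure to reproduce, so the check sets the sections side by side and then sizes the possible distortion.

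**Step 1: objective against analysis.** Section 4.4 states a tolerability aim, 5.4 and 9.2.4 collect the data, and 11.4.5 says there is no safety analysis. These cannot all stand.

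**Step 2: path of a man who tolerates caffeine badly.** Section 8.5 counts three sessions, the first being screening and familiarization.

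- Caffeine first: he takes it in session 2. If he is withdrawn, he has no session 3, and under 8.5 his data are destroyed.
- Caffeine second: he takes it in session 3. If he is stopped before the end, he has not completed the protocol, and 11.4.1 removes him.
- In either order, 11.5 replaces him.

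Only a man whose side effects do not stop him from completing stays in the data.

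**Step 3: how large the distortion could be.** Inputs: 36 men in 3 groups and at least 10 data sets per group (section 11.2).

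- Men per group: 36 / 3 = 12. Spare men per group: 12 − 10 = 2.
- If both spare men left because of caffeine side effects and no completer had any, the true proportion is 2/12 = 16.7%. The completers show 0/10 = 0%.
- If one man left and was replaced, the true proportion is 1/11 = 9.1%, again shown as 0/10.

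These are illustrations. The synopsis and section 6.2.1 plan 30 men, not 36, and replacement under 11.5 leaves the number dosed open.

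**Step 4: precision after the change.** With no events among n men, the exact (Clopper-Pearson) two-sided 95% upper limit is 1 − 0.025^(1/n).

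- One group, n = 10: 1 − 0.025^(1/10) = 30.8%.
- Both spinal cord injured groups together, n = 20: 1 − 0.025^(1/20) = 16.8%.

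These limits come from the sample size and remain after the fix. The fix removes the selection and leaves the imprecision.

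**The case against.** The strongest defence is that the practical consequence is small. This is a low-risk Category A pilot with single doses. Side effects go on the CRF, section 10.1 has all serious adverse events documented, and heart rate is monitored with a doctor available (5.4). Section 11 also makes a general promise: "Descriptive statistics, i.e. median, 25/75% quartiles, 95% confidence intervals and range, will be used". On this view 11.4.5 may mean only that no significance test is planned for safety. The archiving rules also pull against destruction, so the records might survive in practice.

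Much of this stands, and it keeps the point minor. It does not remove the contradiction. The general sentence does not mention safety, the section that does says the reverse, and nothing in 11.4.5 limits it to inferential tests. Archiving in 12.1.3 and destruction in 8.5 give opposite instructions, and neither is said to prevail. Even if the records were kept, 11.4.1 would still confine the analysis to completers.

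A reader might go further and infer that the heart-rate outcome in section 5.3 is also wrong. It compares heart rate during an all-out test, where heart rate may follow power output, and section 11.4.3 names change comparisons for other measures ("Changes in tidal volume, blood pressure and epinephrine and norepinephrine blood concentration from baseline to post-treatment values will be compared") but not for resting heart rate. The documents do not support calling that an error:

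- The exercise comparison is randomised and within-subject, so it validly estimates caffeine's total effect on exercise heart rate. Section 5.3 claims no more: "As caffeine acts as a stimulant heart rate may be altered after the ingestion of caffeine compared to placebo".
- Section 9.2.3 says heart rate "is measured during the HRV measurement and during the performance testing", and the synopsis lists heart rate without confining it to exercise.
- Section 11.4.3 is not a closed list; it also leaves out RPE and exercise heart rate, both promised in 5.3.
- Sizing a workload effect needs a slope the protocol does not give. For the 7.59 W difference in section 6.2.1, an assumed 0 to 0.6 beats/min per W gives 7.59 × 0 = 0 to 7.59 × 0.6 = 4.6 beats/min, a range that includes no effect.

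A reader might also infer that side effects go unrecorded or that acute problems would be missed. Sections 5.4, 9.2.4 and 10.1.2 show otherwise.

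**Conclusion.** The point holds, and it is minor. Section 11.4.5 contradicts section 4.4 and the side-effect questions in 5.4 and 9.2.4. Followed as written, the protocol gives either no tolerability result or, if one is drawn from the analysed data sets, one that omits the men who tolerated caffeine worst.

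The contradiction rests on the text alone. The size of the selection is not known. The figure of 17% shown as 0% assumes 12 men dosed per group, both spare men lost to caffeine side effects, and no side effects in completers. Nothing in the documents says this will happen; it shows only that the rules would allow it to go unseen.

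**What to change.** **Section 11.4.5.** Replace the present entry with a descriptive summary: number and proportion of men with gastrointestinal and other side effects, by treatment (caffeine, placebo) and subject group, with exact 95% confidence intervals. Include everyone who took at least one dose, counting each man under the treatments he actually took. State that the completer rule in 11.4.1 does not apply to this summary.

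**Section 8.5.** Exempt side-effect records and the reason for withdrawal from destruction. This also reduces the conflict with 12.1.3.

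**Cost.** An entry in 11.4.5 and a line in 8.5, with no new measurement or visit. Side-effect records of withdrawn men must be kept, and the estimates will be imprecise at this sample size. A caffeine-versus-placebo comparison of the change in resting heart rate could be added as exploratory, since those values are already recorded, but nothing here requires it.

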| Objective(s): | In general, we are interested in the differences between the heart rate variability before and after caffeine supplementation and if exercise performance is enhanced using this type of supplementation. Another objective is to see whether there are differences between abled-bodied and disabled subjects as subjects with spinal cord injury have an impairment of the autonomic nervous system. |
| Outcome(s): | Primary outcome parameters are differences in heart rate variability and power output in the exercise performance test between caffeine and placebo trial. Secondary outcome parameters are epinephrine and norepinephrine concentration before and after caffeine supplementation, heart rate, tidal volume, lactate concentration before and after the exercise testing, as well as rating of perceived exertion after the exercise performance test. |
| Study design: | Randomised, double-blind, placebo controlled trial (RCT); pilot study |
| Inclusion / Exclusion criteria: | Inclusion: healthy, non-smoker, minimal 3x45 min physical activity per week, tetraplegic (C5 to C7) or paraplegic (sub Th8), AIS A, termination of first rehabilitation and more than 6 months after trauma.  Exclusion: drugs or supplements which influence heart rate variability, diabetes |
| Measurements and procedures: | Heart rate variability (HRV) is measured using a Polar heart rate monitor. After a 10min rest, HRV is measured during a 5 min phase in supine position and afterwards during a 6 min time period in sitting position. These measurements are conducted before the ingestion of the supplement, before the exercise performance test and after the exercise performance test.  Epinephrine and norepinephrine concentrations are measured before supplementation and one hour after supplementation (venous blood withdrawal).  Resting tidal volume is measured during the measurements of HRV.  Power output during the 3 min exercise performance test is analysed.  Lactate concentration is measured before and after the exercise performance testing taking a capillary blood sample.  Blood pressure is measured immediately before every HRV measurement.  Rate of perceived exertion is measured after the warm up and after the exercise performance test. |
| Study Product / Intervention: | Caffeine: 6 mg/kg body mass dosage, supplement will be ingested 1 hour before the exercise performance test respectively 45 min before the HRV measurement. |

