After these 40 min, the second HRV measurement starts. The process of this measurement is exactly the same as for the first HRV measurement. They lay down for a 10 min rest with blood pressure measurement after 9 min. Afterwards again a 5 min HRV measurement in supine position and a 6 min measurement in sitting position will be performed. Tidal volume is measured during this HRV measurement.

When this second HRV measurement session is finished, a second blood withdrawal has to be taken. That means, one hour after the ingestion of either placebo or caffeine, catecholamines are analysed for a second time. After blood sampling, the warm up can start. After the standardised warm up lactate concentration of the blood is analysed taking 10 µl of blood from the earlobe using a blood lactate analyser (Biosen, EKF diagnostic, Cardiff, Great Britain) for analysis. The subject will be asked to evaluate the warm up by rating of the perceived exertion (following the Borg scale from 6 to 20). Then the 3 min exercise test can start. During this test, respiratory parameters will be measured using a device to measure oxygen consumption (MetaMax 3B,Cortex Biophysik GmbH, Leipzig, Germany). Just after having finished these 3 min of exercising, for a second time lactate concentration will be measured and again they have to rate the exertion using the Borg scale (6 to 20).

After a short 5 min break the third HRV measurement starts. Again HRV will be measured during a 5 min time in supine position and a 6 min time in sitting position. Tidal volume will be measured during the whole HRV measurement. With this HRV measurement the first test session is finished and a second test session will be conducted at least more than two days later in a randomised order.

The first visit will take 30 min. The screening and familiarization trial will be finished in around 75 min. For the two test sessions the subject has to be at the Sports Medicine for about 90 min.

In the following chart, the two 90 min test sessions are visually displayed.

[figure not shown]

As we know from previous studies conducted with disabled subjects, the level of the lesion is one critical point. Therefore, we tried to include subjects with almost the same lesion level and sensory and motor complete lesion. This could help us to have more homogenous groups of different populations.

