## Assessments of outcomes

**HRV:** Measurement of the time interval between the separate heart rates using a Polar heart rate monitor (Polar, Kempele, Finland). Data is directly saved as R-R-Interval and will be transferred later on a computer for analysing the data. Heart rate variability will be analysed with the Kubios Software (University of Eastern Finland, Kuopio, Finland). Measurement will be done three times each in supine (for 5 min) and in sitting (for 6 min) position.

**Exercise performance test:** Assessment of power output. The subject will perform a 3 min all out performance test on an arm crank ergometer (Lode, Angio V2, Netherlands).

**Catecholamines:** Measurement of the concentration of epinephrine and norepinephrine in the blood. The blood samples are taken at the crook of the arm and they will be analysed later by Synlab in Lucerne for assessing the concentration of epinephrine and norepinephrine.

**Blood pressure:** Measurement of the systolic and diastolic arterial pressure using a blood pressure monitor (boso medistar S, Bosch + Sohn GmbH, Jungingen, Germany).

**Heart rate:** Heart beats per minute will be measured with the heart rate monitor (Polar, Kempele, Finland) and a heart rate belt (Polar, Kempele, Finland).

**Rate of perceived exertion (RPE):** This parameter is assessed by using the Borg scale from 6 to 20, whereas 6 represents no physical exertion and 20 represents a maximal exertion.

**Tidal volume:** This parameter measures the volume between inspiration and expiration. The volume is assessed by a breathing mask and a spirometer (MetaMax 3B,Cortex Biophysik GmbH, Leipzig, Germany).

**Lactate:** Measurement of the concentration of lactate in the capillary blood. The blood samples are taken at the ear lobe and will be directly analysed using blood lactate analyzer (Biosen, EKF diagnostic, Cardiff, Great Britain).

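### Perceived exertion is compared only after an all-out test, so an unchanged rating cannot be read as no effect of caffeine; the warm-up rating already collected should be compared too

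*Protocol*

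**What the plan says.** Section 5.3 (Other Outcomes of Interest) defines the RPE outcome: "We will compare the RPE after the exercise performance test between the two intervention trials (placebo vs. caffeine". The expected direction is stated there too: "it is possible that RPE is lowered after the ingestion of caffeine compared to placebo", on the ground that caffeine reduces pain. The synopsis names the same time point but lists RPE among the secondary outcomes: "as well as rating of perceived exertion after the exercise performance test".

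The test is described in section 9.2: "The subject will perform a 3 min all out performance test on an arm crank ergometer". Sections 9.2 and 9.2.3 define 20 on the Borg scale as maximal exertion.

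Two ratings are taken per session. Section 9.2.3: "The RPE will be assessed after warming up and after the 3 min performance test". Section 6.1 places the first one after the second blood sample, about an hour after the capsules: "The subject will be asked to evaluate the warm up by rating of the perceived exertion". It calls the warm-up standardised ("After the standardised warm up lactate concentration of the blood is analysed") but gives no load or duration. Under lactate, section 5.3 adds a check that the warm-up was not too hard and was alike in the two trials.

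The protocol defines no treatment comparison of the warm-up RPE. Section 11.4.3 (Secondary Analyses) does not mention RPE at either time point.

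**The concern.** The hypothesis is that the same exercise feels easier after caffeine. That is simplest to test when the work is the same under both treatments and the rating is free to move. The post-test rating may meet neither condition. In an all-out test the man decides how much work he does, and whether caffeine changes that work is itself a primary question (sections 5.1 and 11.1). The instruction is also to reach maximal exertion, which is the top of the scale.

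At stake is the meaning of a null result. If the two sessions give similar post-test ratings, a report could conclude that caffeine does not alter perceived exertion in tetraplegic, paraplegic or able-bodied men, when the data cannot support that. A rating at a load meant to be equal is already being collected and could help.

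**Working it through.** **Step 1: what a post-test RPE can show.** Section 5.3 gives two accounts of the same mechanism. Under RPE, less pain lowers the rating. Under lactate, less pain may let the man push harder, with higher lactate as a result. Both can be true, and they lead to different ratings. The possible results are:

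- RPE lower, power the same or higher: supports reduced exertion.
- RPE lower, power lower: may only reflect less work.
- RPE unchanged, power higher: compatible with reduced exertion turned into more work.
- RPE unchanged, power unchanged: compatible with no effect or, if ratings are near 20, with an effect cut off by the scale.

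So an unchanged RPE is ambiguous without the power output. This step needs no RPE data.

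**Step 2: the limit set by ties.** The protocol states no figure for RPE, so there is none to reproduce. Inputs: at least 10 data sets per group, groups analysed separately (11.4.1); significance at p < 0.05 (section 11); two-sided alternatives (11.1). Assumption: RPE is tested like the other outcomes, by the signed-rank test, here in exact form with zero differences dropped. With k non-zero differences the smallest two-sided p is 2/2^k, reached only when all k have the same sign.

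- 4 of 10 men tied, k = 6: 2/64 = 0.031.
- 5 of 10 men tied, k = 5: 2/32 = 0.0625.

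With five or more tied men, p < 0.05 cannot be reached even if every remaining rating falls.

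**Step 3: how near 20 the ratings must be for this to matter.** The protocol gives no RPE mean, SD or share of men at 20, so the level was varied. Assumptions: 10 men, between-subject SD 1.0, within-trial SD 0.7, ratings rounded and capped at 20, exact signed-rank test, 1,500 simulated trials per row. The mean is the placebo mean before capping.

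| Mean | Power, true effect −1 | Pairs both at 20 (effect −1) | Mean difference seen (effect −1) | Power, true effect −1.5 |
|---|---|---|---|---|
| 17 | 0.60 | 0% | −1.00 | 0.94 |
| 18 | 0.60 | 1% | −0.98 | 0.94 |
| 19 | 0.53 | 9% | −0.88 | 0.91 |
| 20 | 0.32 | 32% | −0.67 | 0.80 |
| 21 | 0.04 | 64% | −0.35 | 0.25 |
| 22 | 0.00 | 89% | −0.11 | 0.01 |

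Far from the ceiling (means of 11 to 13) power is about 0.60 for an effect of −1 and 0.94 for −1.5, the same as at 17 to 18. The loss begins at about 19, is marked at 20 for the smaller effect, and is near total above that.

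**Step 4: what the warm-up rating could add.** It is taken at a load meant to be equal in both sessions and, if the warm-up is moderate, away from the ceiling. If the effect there were also −1, power would be about 0.60 under the same assumptions. Nothing in the protocol supports or refutes an equal effect at warm-up.

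**The case against.** A reader might infer that the Borg scale will be at its ceiling under both treatments and that the comparison is therefore biased to a null result whatever the truth. The protocol does not support this. It defines 20 as maximal exertion but gives no ratings, and Step 3 shows almost no loss at means of 17 to 18. Five ties in ten is an illustration, not an estimate. Section 11.2 plans 36 men, so up to 36/3 = 12 per group, where seven ties would be needed to leave only five differences. The signed-rank test is not assigned to RPE in 11.4.3, and an analysis plan that is not at hand may settle the method. The limit in Step 2 also belongs to the exact test with zeros dropped. All of this stands, and it reduces the ceiling to a risk that depends on the data.

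A reader might also infer that the warm-up rating is the informative one and should replace the post-test rating. That goes too far. The warm-up load is not stated, the lactate check implies it should not be hard, and a short, easy warm-up may cause little pain for caffeine to relieve. Exertion in the performance test is a legitimate question of its own.

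Finally, power output is measured in the same test, so unchanged RPE with higher power can be interpreted. That is right, but 5.3 compares RPE on its own and does not call for this joint reading.

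**Conclusion.** The point holds as a minor improvement. Section 5.3 ties the RPE comparison to a test in which effort is maximal by instruction and the work may differ between treatments. An unchanged post-test RPE therefore cannot by itself be taken as no effect of caffeine on perceived exertion. This conclusion rests only on the protocol's own description.

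The loss of power is conditional. Under the assumptions in Step 3 it is negligible at means of 17 to 18. At 20, power falls from about 0.60 to 0.32 for a one-point effect and from 0.94 to 0.80 for an effect of 1.5 points. Above 20 it is severe. The protocol does not show where these men will lie, nor that the three groups will lie at the same level.

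RPE is an outcome of interest in 5.3 and secondary in the synopsis. Neither primary hypothesis is affected.

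**What to change.** In section 5.3, add a caffeine versus placebo comparison of the RPE already collected after the standardised warm-up. State that each man's warm-up load and duration are kept identical in both sessions.

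Keep the post-test RPE, and say that it will be interpreted jointly with power output from the same test and not taken alone as evidence of no effect. Reporting how many men give the same rating in both sessions, and how many rate 20 in both, would show whether the scale limit was reached.

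The cost is wording: both ratings are already taken at both sessions. The downside is one more exploratory comparison, made at a submaximal load that may be too light to show an effect.
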